#### Data analysis

In order to meet the objectives of this trial, structural and functional connectivity data will be processed in two different ways. First, we will compare measures, obtained at baseline (W0), between ‘responder’ and ‘non-responder’ patients submitted to active rTMS to identify potential brain biomarkers associated with rTMS response. Secondly, we will compare these same data, before versus after active rTMS, between groups of ‘responders’ and ‘non-responders’ to determine explanatory markers of active rTMS-induced AVH improvement. For both steps, we sought to show a significant difference between ‘responders’ and ‘non-responders’. Thirdly, additional exploratory analysis will be performed on clinical, neurophysiological, neuropsychological, and biological measures.

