## Abstract

**Background:**

The potential of non-invasive repetitive transcranial magnetic stimulation (rTMS) to improve auditory verbal hallucinations (AVH) in schizophrenia patients has been increasingly explored over the past decade. Despite highly promising results, high inter-individual variability of clinical response and ineffective outcomes in a significant number of patients underscored the need to identify factors associated with the clinical response to rTMS. It should help improve the efficacy of rTMS in patients with medication-resistant AVH, and allow a better understanding of its neural impact. Here, we describe an exploratory study protocol which aims to identify structural and functional brain biomarkers associated with clinical response after an rTMS treatment for medication-resistant AVH in schizophrenia.

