**Discussion:**

The aim of this research project is to identify and assess the biomarker value of MRI-based structural and functional biomarkers predicting clinical response to rTMS for AVH in schizophrenia patients. The outcome of the trial should improve patient care by offering them a novel suitable therapy and deepen our understanding on how rTMS may impact AVH and develop more effective therapies adapted to individual patient needs.

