Variability of clinical response to rTMS has been explained by brain connectivity differences subtending functional [20] and/or structural [21–23] interactions. Nonetheless, to date, very few studies have aimed to further characterize the detailed determinants of this variability. A better understanding of this phenomena bears the potential to increase the effectiveness of rTMS-based treatments and promote the development of individualized therapeutic approaches tailored to the specificities of each patient. The identification of predictive and explanatory biomarkers of clinical response to rTMS is an expanding domain with the potential to improve therapeutic plans offered to patients, while improving our understanding of underlying rTMS mechanisms on pathological symptoms such as AVH. Herein, we will test the impact of active rTMS 1 Hz stimulation delivered to the left TPJ on AVH severity scores and use such outcomes to quantify interindividual clinical response variability and test the predictive and explanatory value of a series of magnetic resonance imaging (MRI)-based functional and structural biomarkers assessing interregional interactions. A large battery of clinical, neuropsychological, and motor excitability neurophysiological assessments as well as molecular biology serum assays will be performed in parallel to better understand the determinants of AVH in schizophrenia and pinpoint rTMS therapeutic mechanisms. We hypothesize that rTMS treatment for AVH will show large interindividual response variability, providing a unique opportunity to identify MRI-based structural and functional connectivity biomarkers of positive clinical response to focal neurostimulation.

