### Outcome measures

#### Primary outcome measures

Our primary aim is to identify brain connectivity differences between patients ‘responders’ and ‘non-responders’ to rTMS treatment. To cluster patients as ‘responders’ or ‘non-responders’, the clinical response to rTMS will be defined as a decrease of 50% or more in the HCS from baseline (W0) at the end of the active rTMS stimulation (W3). This definition is similar to that employed in previous studies [27, 28]. The HCS is described in the Clinical assessments section in the Secondary outcome measures paragraph and will allow analysis of the dataset in search of biomarkers associated with rTMS response, in particular structural and functional connectivity biomarkers.

To identify structural connectivity biomarkers to rTMS therapeutic response, we will compare DWI datasets, acquired at baseline, between ‘responder’ and ‘non-responder’ patients to rTMS. More precisely, we will consider fractional anisotropy (FA) levels along tracts of interest that will be reconstructed from probabilistic tractography algorithms. FA levels will be obtained at several equidistant points along the tract of interest [29]. This procedure will allow evaluation of the existence of global or focal (close to the stimulation site) white matter integrity alterations between ‘responders’ and ‘non-responders’. Tracts of interest will include the fasciculi that are involved in the language network (connections between TPJ and Broca areas, so called the arcuate fasciculi on each hemisphere, and transcallosal connections between the TPJ or Broca areas), and those that are part of the DMN (connections between the superior parietal cortex and prefrontal areas within each hemisphere; transcallosal connections between superior parietal cortex or prefrontal areas). FA values along each tract will be obtained at baseline (W0) and after rTMS treatment (W3) for ‘responders’ and ‘non-responders’.

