Once tracts are reconstructed, one complementary measure will be considered. FA values will be measured along the tracts of interest. Along-tract measures of FA will be obtained on the basis of B-spline resampling of the fibers and averaging the FA values for each individual fiber on a given location (elastic model with 30 points in space at analogous anatomical locations in each individual) [29]. For instance, for the language network, the posterior location will be defined on the ROI of the TPJ, whereas the anterior location will be defined as the level of the ROI of the Broca areas. Mean FA values will be calculated at each point of the mean fiber along the *y* axis to check for local differences at specific points of the tract. A linear mixed-effects model will be applied serially for each tract and permutation methods will be performed to adjust the *p* values and control the Type 1 error.

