## Discussion

Several meta-analyses support significant reduction of AVH severity in schizophrenia following a multi-day 1 Hz rTMS regime [12–19], spurring hopes for rTMS for this indication. Nonetheless, the high level of interindividual variability in clinical responses has weakened enthusiasm about its clinical efficacy and the topic remains debated. In this context, the identification of biomarkers predictive of positive clinical response could help clarify the situation and provide more effective, suitable, and customized treatments for AVH in schizophrenia. Moreover, by identifying patients who are most likely to respond before therapy is applied, clinical indications could be fine-tuned and, thus, general outcomes could be improved. In our trial, functional and structural neuroimaging datasets recorded prior and following the rTMS therapy will be employed to better characterize mechanisms underlying the emergence of AVH, evaluate the impact of a multiday rTMS regime, and gauge ability to drive enduring recovery.

The protocol proposed for our trial follows previously established recommendations on therapeutic uses of rTMS for the treatment of AVH, using 1 Hz rTMS over the left TPJ region [66]. However, to date, no clear guidelines exist to titrate other stimulation parameters, such as rTMS intensity (established between 90% and 100% of the MT) or the number of total sessions (or cumulated sessions per day) necessary to achieve stable recovery in the shortest possible period (10 sessions over 1–2 weeks remain the most common protocol), which vary greatly across studies [66]. Moreover, no established guidelines seem to exist yet with regards to the maximal number of pulses to be delivered per session. Nonetheless, to our knowledge, no study included in the guidelines for therapeutic use of rTMS [66] or cited in the 11 meta-analyses addressing the effect of rTMS on auditory hallucinations in schizophrenia from 2007 to 2018 [13–18, 67–69] seem to use more than 1200 pulses per session. To remain consistent with prior literature and convince the Institutional Review Board of the safety of our interventions we took the decision to align ourselves with established recommendations or prior peer-reviewed publications in the field.

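### The protocol says it will test the predictive value of MRI markers, but the planned group comparisons show association only and never measure or validate prediction

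*Protocol article*

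**What the plan says.** The article words its aim at two levels.

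- **Predictive wording.** The Discussion paragraph of the Abstract gives the aim as to "identify and assess the biomarker value of MRI-based structural and functional biomarkers predicting clinical response to rTMS". The Background says the study will "test the predictive and explanatory value of a series of magnetic resonance imaging (MRI)-based functional and structural biomarkers". The main Discussion foresees better use of the treatment "by identifying patients who are most likely to respond before therapy is applied".
- **Association wording.** The Abstract's Background says "we describe an exploratory study protocol which aims to identify structural and functional brain biomarkers associated with clinical response". Primary outcome measures says "Our primary aim is to identify brain connectivity differences between patients" who do and do not respond. Aims and hypotheses likewise asks whether connectivity patterns differ between the two groups.

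The Data analysis section then says how the objectives will be met. The MRI data are compared between responders and non-responders at baseline, and again as before-versus-after change. The target is common to both: "For both steps, we sought to show a significant difference between" the two groups.

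The methods sections follow this:

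- For along-tract FA, "A linear mixed-effects model will be applied serially for each tract and permutation methods will be performed to adjust the" p values and control Type 1 error.
- For resting-state connectivity, two-sample t tests on z maps.
- For dynamic causal modelling, Bayesian model selection, then one-sample tests within groups and two-sample tests between groups on each connection.

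Response is always the grouping factor and never the outcome being predicted. No AUC, sensitivity, specificity, cut-off or validation is described.

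**The concern.** A test of mean difference asks whether two distributions are shifted. Prediction asks how far they overlap, and so how often a patient would be put in the wrong group. In a small sample, a shift can be significant while the overlap remains large.

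The plan ties success to significance and includes no step that would reveal the overlap. A marker could therefore be reported as predictive on a group difference alone. That matters because the Discussion looks ahead to picking out likely responders before treatment, which is a decision about individuals.

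This is not a detail that a condensed article merely leaves to a fuller plan. The Data analysis section states how the objectives are met and what result is sought, and that result does not reach the predictive part of the aim.

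**Working it through.** **Inputs** (Sample size section): two-group comparison, α = 0.05, power 0.80; 32 active-arm patients, raised to 35 for 10% drop-out; a 40%/60% response split, giving 14 responders and 21 non-responders.

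**The plan's own figure.** The 32 cannot be reproduced, because neither the FA difference nor its SD is given. Solving backwards with a two-sided t test, 32 patients split 16/16 have 80% power at a standardised difference d of about 1.02 (0.99 by the normal approximation). With a 13/19 split, d is about 1.04. The trial is thus sized for a d of about 1.

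**Smallest significant difference, 14 v 21, single unadjusted test.**
d = t(0.975, 33 df) × √(1/14 + 1/21) = 2.035 × 0.345 = 0.70.

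**Conversion to discrimination** (assumes normal distributions with equal variance):

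- AUC = Φ(d/√2)
- Proportion correct at the midpoint cut-off, where sensitivity equals specificity: Φ(d/2)
- Hanley–McNeil standard error: √{[A(1−A) + 13(Q₁−A²) + 20(Q₂−A²)]/(14×21)}, with A the AUC, Q₁ = A/(2−A) and Q₂ = 2A²/(1+A)

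For d = 0.70: A = Φ(0.496) = 0.690, Q₁ = 0.527, Q₂ = 0.564, SE = 0.094. The 95% CI is 0.690 ± 1.96 × 0.094.

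| Observed d | AUC (95% CI) | Correct at midpoint |
|---|---|---|
| 0.70 (just p = 0.05) | 0.69 (0.51 to 0.88) | 64% |
| 1.0 (about 80% power) | 0.76 (0.59 to 0.93) | 69% |

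**Benchmark.** Calling everyone a non-responder is correct in 21/35 = 60%. The midpoint cut-off ignores the 40/60 split. Moving the cut-off by ln(0.6/0.4)/d = 0.405/0.70 = 0.58 SD gives 0.6 × Φ(0.93) + 0.4 × Φ(−0.23) = 66% for d = 0.70, still only about 6 percentage points above the benchmark.

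**At d = 1.0 and 40% response.** Positive predictive value = (0.69 × 0.4)/(0.69 × 0.4 + 0.31 × 0.6), about 60%. Negative predictive value is about 77%. Precision is low: a sensitivity of 10/14 has an exact 95% CI of 42% to 92%, and a specificity of 14/21 has 43% to 85%.

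**Sensitivity to drop-out.** With 13 v 19 analysed, the smallest significant d is 0.74, with AUC 0.70 (0.51 to 0.89) and 64% correct. The conclusion does not change.

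**Allowing for the planned adjustment of FA.** Permutation over the 30 points of a tract raises the threshold. Bonferroni for 30 tests is an upper bound: d = t(1 − 0.05/60, 33 df) × 0.345 = 3.424 × 0.345 = 1.18, giving AUC 0.80 and 72% correct. Points along one tract are correlated, so the real threshold lies between 0.70 and 1.18. Even at the upper bound, 28% are misclassified, and this figure is itself taken from the point that looked best.

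**The case against.** The strongest reply is that the formal objective is association. The study is labelled exploratory, the primary outcome is the baseline FA difference, and the baseline step seeks potential biomarkers associated with response. The planned tests answer that. The predictive wording comes from the Abstract's discussion, the Background and a hopeful passage of the main Discussion. All of this stands, and it limits the point to the predictive aim. A reader might infer that the trial leaves its main question unanswered or that the primary comparison is invalid. The documents support neither.

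A second reply is that permutation controls Type 1 error for FA. This also stands: a chance FA difference is guarded against within each tract. But the adjustment concerns whether a difference exists. It neither measures discrimination nor removes the optimism in the apparent accuracy of a selected marker.

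A reader might also infer that the best of many null markers would look impressive here. In simulation, the best of 30 independent null markers has a mean in-sample AUC of 0.73. The 30 points lie along one tract, however. If neighbouring points correlate at an assumed 0.9 to 0.95, the figure is about 0.67 to 0.69. No AUC is planned either, so this is a caution for any later accuracy claim and not a description of the plan.

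Nor is every planned MRI analysis a two-group test, since the causal-modelling section also has model selection and one-sample tests. These do not measure prediction of response either.

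Finally, about 14 responders are too few for serious prediction modelling. That is true, and it argues for a restrained claim.

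**Conclusion.** The point holds in a limited form. The primary comparison is appropriate to the formal aim and should stay. The further aim of assessing predictive value has no analysis behind it, so a significant group difference would be the only basis for calling a marker predictive.

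The size of the gap: a result that just meets the unadjusted criterion corresponds to an AUC of about 0.69, with a lower limit of 0.51, and about 64% correct against a 60% benchmark. The effect the trial has about 80% power to detect corresponds to 0.76 (0.59 to 0.93) and 69%. These figures assume normality, equal variances and the 14/21 split. They are before any correction for optimism.

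A reader might conclude that an AUC interval excluding 0.5 would settle the matter. It would not: the borderline case above passes that test while classifying little better than the benchmark.

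**What to change.** 1. Keep the primary FA comparison and its permutation adjustment unchanged.
2. Add an exploratory secondary analysis in the active arm with response as the outcome. Name a small set of baseline markers in advance, for example mean FA of the left arcuate fasciculus (the tract behind the sample size) and one connection per network.
3. For each marker, report AUC, sensitivity and specificity with 95% CIs. Cross-validate, with any choice of marker or cut-off made inside the folds. With about 14 responders, selection inside folds will be unstable, so fixing the markers beforehand is preferable.
4. Describe positive results as candidate markers associated with response. Do not claim predictive value from a significant group difference, or merely because the AUC interval excludes 0.5. State that external validation is needed.
5. Bring the wording of the Abstract's discussion and the Background into line with this.

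The cost is slightly more analysis on data already being collected, with no change to recruitment or procedures. The price is wide intervals and a more modest claim. An active-arm analysis also describes response under active stimulation; it cannot separate benefit from rTMS from general prognosis or placebo response, and 10 sham patients give little power to do so.

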#### MRI data analysis

##### Regions of interest (ROIs)

Two spherical ROIs corresponding to the rTMS target (left TPJ) and its homotopic region in the right hemisphere (right TPJ) will be generated using the MarsBaR toolbox (http://marsbar.sourceforge.net/) [53]. Each sphere of a 5 mm radius will be centered at x = − 55, y = − 41, and y = 11 for the left TPJ, and at x = 55, y = − 41, and y = 11 for the right TPJ. MNI atlases will be used to define ROIs containing the nodes of the DMN and the language network. The masks of the left and right frontal inferior gyri and posterior cingulate cortex will be extracted from the WFU PickAtlas (http://fmri.wfubmc.edu/software/PickAtlas). A mask of the corpus callosum will be manually drawn on a T1-weighted MNI template using the Functional Magnetic Resonance Imaging of the Brain (FMRIB) Software Library (FSL 5.0.9, http://www.fmrib.ox.ac.uk/fsl/). For tractography analyses, the same ROI will be de-normalized from the MNI space to the individual space using the inverse transformation obtained from the VBM8 toolbox.

##### Structural connectivity analysis

Diffusion images will be preprocessed using FSL software and then processed for probabilistic diffusion tractography with MRtrix3 software (http://www.mrtrix.org/). Diffusion volumes will be corrected for motion and geometric distortions induced by eddy currents. The constrained spherical deconvolution method will be used to estimate the fiber orientation distribution function (ODF) in MRtrix3 [54]. In the native space of each subject, a seed-to-target analysis will be performed to reconstruct the tracts of interest included in the DMN and the language network (arcuate fasciculus, corpus callosum).

Fiber-tracking maps will be created for each subject by using FSL software (data preprocessing) and MRtrix3 software (diffusion images) [54]. Using a voxel-wise model of diffusion (the Q-ball model), the maximum-likelihood solution for fiber orientation within each voxel will be represented by an ODF on the location of the fiber trajectory. The ODF characterizes the orientation dependency of the diffusion probability density function of water molecules in several possible directions for each voxel. This model can be used to track complex fiber configurations. The ODF information obtained from constrained spherical deconvolution will be used with a suitable fiber-tracking algorithm to infer connectivity of crossing fibers. We will use a probabilistic streamline algorithm with the entire ODF as a probability density function (ODF threshold = 0.1; step size = 0.5 mm x voxelsize; radius of curvature = 1 mm; up-sampling of DWIs, data to 1 mm). In the native individual space, we will perform a seed-to-target analysis from ROIs of the networks of interest (see Region of interest section). These regions will include the bilateral TPJ, the inferior frontal gyri and the corpus callosum. We will use the following probabilistic tractography algorithm: the number of fibers (streamlines) connecting a seed voxel to a target voxel will be calculated by sampling 1 million draws for each fiber connecting the seed to the target. The pair-wise connections of the DMN and the language networks will be reconstructed for each subject.

Once tracts are reconstructed, one complementary measure will be considered. FA values will be measured along the tracts of interest. Along-tract measures of FA will be obtained on the basis of B-spline resampling of the fibers and averaging the FA values for each individual fiber on a given location (elastic model with 30 points in space at analogous anatomical locations in each individual) [29]. For instance, for the language network, the posterior location will be defined on the ROI of the TPJ, whereas the anterior location will be defined as the level of the ROI of the Broca areas. Mean FA values will be calculated at each point of the mean fiber along the *y* axis to check for local differences at specific points of the tract. A linear mixed-effects model will be applied serially for each tract and permutation methods will be performed to adjust the *p* values and control the Type 1 error.

##### Resting-state functional connectivity analysis

Statistical parametric mapping software (SPM8, Wellcome Department of Cognitive Neurology, London, UK) will be used for image processing (http://www.fil.ion.ucl.ac.uk/spm/). The functional images will be interpolated in time to correct for phase advance during volume acquisition, and will be realigned with the first image of each session. The anatomical image and the realigned functional images of each subject will then be normalized to a common standard space by using the MNI template (DARTEL [55]). The functional data will be spatially smoothed with a 4-mm full-width at half-maximum Gaussian filter and temporally filtered (0.01–0.08 Hz) with a 128-s period high-pass filter.

Functional connectivity analysis will be performed [56–59]. The correlations in spontaneous BOLD fluctuations reflect the inter-regional correlations in neuronal variability [60, 61]. The averaged time course will be obtained from a previously defined ROI (posterior cingulate cortex for the DMN, TPJ for the language network). The correlation analysis will be performed in a voxel-wise way to generate the functional connectivity map. The correlation coefficient map will be converted into a *z* map by Fisher’s *r*-to-*z* transform to improve the normality [62] (Data Processing Assistant for Resting-State fMRI [63], http://www.restfmri.net). For each network of interest (DMN, language network), the second level analysis will be performed using a two-tailed, two-sample *t* test on the *z*-score maps to show group differences on connections of the DMN and language networks.

Effective connectivity analysis will be performed using DCM with the DCM10 routine implemented in Statistical Parametric Mapping software 12. The first eigenvectors will be extracted from the ROIs representing the DMN and language networks (see ‘Regions of interest’ section). The a priori models will be based on anatomical connections, considering a fully connected model of the DMN and language network. Intrinsic connectivity will be defined as the endogenous connectivity parameter without driving input [31]. The intrinsic connectivity values will be obtained for each subject in the best model of each network that will be considered for group analysis. Bayesian model selection [64, 65] will be used to determine the best model between unilateral and bilateral connections. Expected posterior model probabilities and exceedance probabilities will be computed. The group analysis on the DCM parameters will only include the model that will best fit the data. Within each group, one sample *t* test will be conducted to examine whether the parameters of the model that best fits the data will have significant non-zero values. Two-sample *t* tests will be used to identify group differences in intrinsic connectivity on each connection. The same will be performed for the DMN to examine whether rTMS has a specific effect on the language network or a more global effect on attentional mechanisms.

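### The dynamic causal modelling analysis asks whether rTMS acts on the language network specifically or more globally, but plans only separate tests in each network and no comparison between them

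*Protocol article*

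**What the plan says.** The point lies in the effective-connectivity part of the protocol article's section on resting-state functional connectivity analysis (dynamic causal modelling, DCM).

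- Each network is modelled separately: "The intrinsic connectivity values will be obtained for each subject in the best model of each network that will be considered for group analysis".
- Two-sample t "tests will be used to identify group differences in intrinsic connectivity on each connection".
- The paragraph ends with the specificity question: the same "will be performed for the DMN to examine whether rTMS has a specific effect on the language network or a more global effect".

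The seed-based analysis in the same section has the same layout: "For each network of interest (DMN, language network), the second level analysis will be performed using a two-tailed, two-sample" t test on the z maps.

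The DCM paragraph does not name the groups. The Data analysis section does: "Secondly, we will compare these same data, before versus after active rTMS, between groups of" responders and non-responders. The Sample size section expects 14 responders and 21 non-responders in the active arm. The section on demographic and clinical data sets the significance level for all tests at 0.05.

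Nowhere does the article describe a language-versus-DMN comparison, a group-by-network interaction, or a margin below which a DMN effect would count as absent.

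**The concern.** The article states a question (specific or global) and the procedure meant to answer it (repeat the tests in the DMN). Specificity is a claim about the difference between two effects, and the procedure never estimates that difference. If the reader has only two sets of p values, the pattern that points to specificity is significance in the language network without significance in the DMN. That pattern also arises by chance when both networks differ equally between the groups, because at this sample size a real DMN difference can easily be missed.

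What is at stake is a mechanistic statement about where rTMS acts. It could be made, or withheld, for reasons unrelated to whether the networks behave differently.

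**Working it through.** **Inputs**
- Group sizes (Sample size): 35 × 0.40 = 14 responders and 35 × 0.60 = 21 non-responders. This reproduces the stated split.
- Level: 0.05. Two-sidedness is stated for the seed-based tests and assumed here for DCM.
- Effect size for DCM parameters: none is given, so 0.3 to 1.0 SD is assumed.
- Correlation between the network measures: none is given, so 0 to 0.5 is assumed.

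**The plan's own sample-size figure.** The 32 active patients before drop-out cannot be reproduced, because no FA difference or SD is stated. Solving backwards, (1.960 + 0.842) × √(1/n₁ + 1/n₂) gives 0.99 SD at 16 v 16 and 1.01 SD at 13 v 19. This concerns baseline FA, not DCM parameters.

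**Step 1: one test per network, 14 v 21.** The noncentrality is d / √(1/14 + 1/21) = d / 0.345, with 33 degrees of freedom and a critical t of 2.03.

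| True difference | Power | Missed |
|---|---|---|
| 0.3 SD | 13.5% | 86.5% |
| 0.5 SD | 29.1% | 70.9% |
| 0.8 SD | 61.4% | 38.6% |
| 1.0 SD | 80.3% | 19.7% |

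At 0.5 SD the miss rate is 73.0% with 32 completers (13 v 19). It is 72.4% if the groups were active v sham (35 v 10), so the choice of grouping matters little.

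**Step 2: the same true effect in both networks** (simulation, 40,000 trials, still one test per network).

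| Effect in both | Correlation | DMN non-significant, given language significant | Language significant and DMN not, all trials | Direct contrast rejects |
|---|---|---|---|---|
| 0.5 SD | 0 | 71% | 20% | 5% |
| 0.5 SD | 0.5 | 49% | 14% | 5% |
| 0.8 SD | 0 | 38% | 23% | 5% |
| 0.8 SD | 0.5 | 26% | 16% | 5% |
| 1.0 SD | 0 | 20% | 16% | 5% |
| 1.0 SD | 0.5 | 14% | 11% | 5% |

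By symmetry, the DMN-only pattern is equally frequent.

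**Step 3: per-connection testing, as the article plans it.** The Outcome measures section lists 4 language nodes and 8 DMN nodes. If all were modelled and fully connected (an assumption), there would be 4 × 3 = 12 and 8 × 7 = 56 directed connections. Call a network positive if at least one connection is significant, and put 0.5 SD in both networks. In the settings simulated, the chance of no DMN result given a language result was:
- about 0–11% with an effect on every connection and no correction;
- about 27–43% with an effect on every connection and Bonferroni within network;
- about 39–86% with an effect on one connection only.

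These are not bounds. They move with the number of connections, how many carry an effect, and any correction.

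The opposite error is also possible. With no DMN effect and independent uncorrected tests, the chance of at least one significant connection is 1 − 0.95¹² = 46% for 12 tests and 1 − 0.95⁵⁶ = 94% for 56. Correlation between connections would lower both figures.

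**Step 4: power of a direct contrast.** The difference language minus DMN has SD √(2(1 − ρ)). For 1.0 SD in language and none in the DMN, the standardised effect is 1.0 / √(2(1 − ρ)), which is 0.71, 0.85 and 1.00 at ρ = 0, 0.3 and 0.5. Power at 14 v 21 is 51%, 66% and 80%.

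**The case against.** The strongest objections are these.

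- **The decision rule is not written down.** The article says only that the question will be examined. A reader might infer that the authors have committed to treating a non-significant DMN test as proof of specificity. The text does not say so, and the estimates could be compared descriptively. This stands as a limit on the charge. It does not remove the problem, because the procedure described contains nothing that measures the difference between networks.
- **It may be detail left to a fuller document.** Much interpretation is. Here, however, the article names both the question and the method, and the method cannot answer the question. That is a stated choice, not a gap.
- **The 71% does not describe the plan.** This stands. A reader might take it as the rate of false specificity claims. It assumes one test per network and 0.5 SD, whereas the article tests each connection. Step 3 shows rates from near zero to above 71%. At about 1.0 SD, the size implied by the FA calculation, a single test misses 20%.
- **Specificity is a small part of the trial.** This also stands. It appears in one clause, and not among the two aims, the three analysis steps or the sample-size basis. The study calls itself exploratory.
- **The seed-based tests pose no specificity question.** Correct. They show the same layout and carry no weight of their own here.
- **A network average can cancel directed parameters that move in opposite directions.** Correct, so the summary needs its signs fixed beforehand.

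**Conclusion.** The point holds in limited form. The DCM paragraph poses a specific-or-global question and describes only separate per-connection tests in each network. A language result beside a non-significant DMN result would not establish specificity.

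The size of the error cannot be fixed from the document. The illustrative miss rates of 71%, 39% and 20% at 0.5, 0.8 and 1.0 SD rest on assumed effects and a single test per network. Under per-connection testing the error could be much smaller or larger, and could run towards a false global reading. The logical fault depends on none of these figures.

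The document does not support a claim that the trial's main conclusion is at risk. The analysis is secondary and exploratory, and the primary comparison of baseline FA is untouched. The change is worth making because it is cheap.

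**What to change.** In the DCM paragraph, base any statement about specificity on one pre-specified group-by-network contrast:

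- For each active patient, form a standardised summary of connectivity in each network. Name the connections and fix their signs in advance, so that opposite changes do not cancel.
- Take language minus DMN. Use the W3 − W0 change, since the question concerns an effect of rTMS.
- Compare this difference between responders and non-responders, and report the estimate with a 95% confidence interval beside the two network estimates and their intervals.
- If the contrast is not significant, say that specificity has not been established.
- Keep the per-connection tests as descriptive, and state that a non-significant DMN result will not be read as absence of an effect.

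The cost is some analysis wording and one extra contrast on data already to be collected. Sample size and visits do not change. The drawback is that specificity becomes harder to claim. Even with 1.0 SD in language and none in the DMN, power is about 51–80% for between-network correlations of 0 to 0.5. If the DMN also differs by 0.5 SD, power falls to about 17–29% over the same correlations.
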